### Data collection methods

Structured interviews administered at the health facility and at participants’ farms or homes were conducted by trained research assistants who used a handheld computer tablet for data entry (Morotola™ Xoom Android Tablets operating Open Data Kit (ODK) Collect (Hiarlaithe et al. 2014). Research assistants conducted structured interviews in the local language (Dholuo) or English and completed paper-based data collection forms for the majority of baseline data collection (Table 1). Forms were later entered into the tablet using ODK Collect. Research assistants entered subsequent data directly into the tablet. Data for anthropometry (MUAC and BMI), and viral load results were entered into ODK Collect forms (Table 1). Medical history and CD4 determinations were abstracted from patient records and entered into the tablet (Table 1).

### Monitoring

The study team conducted internal monitoring such as form completion and quality control of data entry monthly. Procedures to promote data quality including range and logical checks were built into the data entry program, and we ran a series of additional error checks on the databases following data entry. In addition, we used a rainfall gauge at the two study sites to record total precipitation by month.

### Process evaluation methods

In order to understand the implementation successes and challenges, we conducted a detailed process evaluation alongside the *Shamba Maisha* trial. We interviewed 40 intervention participants and 20 key informants at two time points (3–5 months after study start and study end) to understand successes and challenges with implementation (for a total of n = 120 interviews). Interviews were conducted in English, Dhuluo or Kiswahili, and lasted between 45 minutes and 2 hours. We used a semi-structured interview guides to probe for feedback on recruitment and retention as well the key intervention components (the microcredit loan, the agricultural training, and the use of the hip pump), and elicit suggestions on how to improve each of these components. Interviews were transcribed verbatim and (as necessary) translated into English. Data were managed using Dedoose, (Dedoose Version 5.0.11 et al. 2014) a qualitative software that allows for real-time access to a secured database by a number of people in an analysis team. In line with previous qualitative process evaluations of complex interventions (Hargreaves et al. 2010), we used an inductive-deductive approach. First interviews were coded for broad themes by four researchers, using a structured coding framework developed from topics covered in the interview guide. Next, a second stage of inductive coding allowed sub-themes to emerge. Process evaluation findings are used to suggest how these might help refine the intervention in a future trial.

### Statistical methods

For this baseline manuscript, we compared baseline characteristics between participants enrolled in the intervention and control sites using proportions for categorical variables and means or medians (as appropriate) for continuous variables. An assessment of the distribution (normally or skewed) of continuous variables was performed. Statistical tests for descriptive analyses included chi-square tests for categorical variables, and Wilcoxon rank-sum or t-tests and for continuous variables.

#### Analysis of outcome data

This pilot was not powered for formal significance testing of the intervention effect on primary health, behavioral and gender empowerment outcomes. Rather, analyses will focus on assessing the effects of the intervention on proximal mediating factors (Figure 2), and separately on primary outcomes. Analyses for mediating variables will generally treat scores as continuous measures. For example, food security will be measured using the Household Food Insecurity Access Scale (HFAIS) score at the 1-year visit; change in household economic indicators over the 1-year follow-up period will be measured by subtracting baseline from 1-year follow-up data for household expenditures, consumption and income (from agricultural and other sources). Initial comparisons will be based on group-specific descriptive summaries of observed outcomes and rank-based tests comparing outcomes between groups. We will also use regression methods to compare outcomes between groups and control for baseline characteristics. Analyses for primary health outcomes will proceed similarly, with appropriate choices of model for outcome type. For example, we will use pooled logistic regression for between-group comparisons of rates of viral load suppression, and mixed effects regression to compare changes in CD4 counts between groups. We will also make preliminary assessments of degree of mediation in models for primary outcomes via inclusion of mediating factors, with assessment of direct and indirect intervention effects of key mediating variables (Petersen et al. 2006). Finally, we will also perform intent-to-treat and per-protocol analyses of the pilot data, with the per-protocol subset limited to participants that obtained and used the intervention consistently over the 12-months of follow-up. Although these analyses will likely be underpowered for formal testing purposes, the resulting estimates and confidence intervals will be important for planning for the subsequent RCT.

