**Methods/Design:**

We conducted a pilot cluster randomized controlled trial (RCT) of a multisectoral agricultural and microfinance intervention (entitled *Shamba Maisha*) designed to improve food security, household wealth, HIV clinical outcomes and women’s empowerment. The intervention was carried out at two HIV clinics in Kenya, one randomized to the intervention arm and one to the control arm. HIV-infected patients >18 years, on antiretroviral therapy, with moderate/severe food insecurity and/or body mass index (BMI) <18.5, and access to land and surface water were eligible for enrollment. The intervention included: 1) a microfinance loan (~$150) to purchase the farming commodities, 2) a micro-irrigation pump, seeds, and fertilizer, and 3) trainings in sustainable agricultural practices and financial literacy. Enrollment of 140 participants took four months, and the screening-to-enrollment ratio was similar between arms. We followed participants for 12 months and conducted structured questionnaires. We also conducted a process evaluation with participants and stakeholders 3–5 months after study start and at study end.

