### Intervention model

The primary aim of the pilot study was to test if a multisectoral agricultural intervention improves food security and HIV health outcomes. We hypothesized that the proposed multisectoral agricultural intervention will improve food security, prevent treatment failure, reduce co-morbidities, and decrease secondary HIV transmission risk among PLHIV.

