***Shamba Maisha***
**intervention framework**

### Randomization

We used a two-step process to select two sites from among 68 government health facilities in Rongo, Migori and Nyatike districts supported by Family AIDS Care & Education Services (FACES), a collaboration between the University of California, San Francisco (UCSF), and the Kenyan Medical Research Institute (KEMRI) (Lewis Kulzer et al. 2012). First, we limited to 20 sites where there were an adequate number of PLHIV on ART at the time of the study, and where farming was a primary means of livelihood in the communities. Next, we selected two government health facilities for the pilot randomized controlled trial (RCT) according to the following criteria: a) having adequate numbers of PLHIV on ART with non-overlapping catchment areas; b) having catchment areas that were relatively similar to one another according to rainfall patterns, health, topography and socioeconomic status; and c) meeting practical requirements for the intervention, including acceptable characteristics in topography to enable use of the water pump, having water access year round, and having favorable soil composition to potentiate the intervention. One site was randomly selected as the intervention site and the other the control site by the study’s biostatistician who used a computer random number generator and was not involved in fieldwork. Clinics, healthcare providers, patients, and researchers involved in implementing the study were not blinded to the allocation.

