## Results

### Screening and enrollment

Figure 3 describes study screening and enrollment numbers, along with reasons for participant ineligibility. We screened 142 and 154 adults, respectively at the intervention and control sites. We enrolled 72 and 68 participants at the intervention and control sites, respectively; four participants withdrew from the study, four from the intervention site and zero from the control site. One participant in the intervention arm failed to save the down payment necessary to receive the loan and was subsequently withdrawn from the study. The most common reasons for study ineligibility of screened participants included: did not have access to land or surface water, lived outside the study area, not on ART, and “other” reasons.

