These findings should be considered in light of design limitations. The pilot cluster-randomized design included two sites, and thus will need to be replicated in a larger cluster randomized trial. Second, qualitative process evaluations may suffer from respondent bias, particularly if participants held the impression that researchers were part of the intervention delivery team. We attempted to address this shortcoming by hiring separate in-depth interviewers that were not part of the primary study team. Lastly, the challenges with our microfinance organization made it difficult to assess the full potential of that component of the intervention.

We expect the pilot study will provide critical new evidence regarding the implementation of a multisectoral agricultural intervention aimed to improve food insecurity, household economic indicators and health among HIV-infected persons in rural Kenya. Following evaluation of the quantitative and qualitative results from this study, we plan to scale up this pilot to a cluster randomized trial to definitively assess the effectiveness of this intervention on the health of PLHIV using ART.

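### With one clinic per arm, the planned between-arm tests and confidence intervals cannot contain between-site variation, and the article describes them only as underpowered

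*Protocol article*

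**What the plan says.** The abstract gives the design: "The intervention was carried out at two HIV clinics in Kenya, one randomized to the intervention arm and one to the control arm". The Randomization section confirms that the clinic was the unit allocated: "One site was randomly selected as the intervention site and the other the control site by the study’s biostatistician". Enrolment is reported under Screening and enrollment: "We enrolled 72 and 68 participants at the intervention and control sites, respectively".

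Analysis of outcome data plans rank-based comparisons between groups, regression with control for baseline characteristics, pooled logistic regression for viral suppression and mixed effects regression for CD4 change. It names no site term and does not specify the random effects in the CD4 model. It gives one caution: "This pilot was not powered for formal significance testing of the intervention effect on primary health, behavioral and gender empowerment outcomes". It closes by calling the analyses probably underpowered while adding that "the resulting estimates and confidence intervals will be important for planning for the subsequent RCT".

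The Discussion adds: "The pilot cluster-randomized design included two sites, and thus will need to be replicated in a larger cluster randomized trial". It also says that the future trial, with about eight matched pairs (16 sites), will deal with heterogeneity.

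The aim is worded in more than one way. Intervention model states: "The primary aim of the pilot study was to test if a multisectoral agricultural intervention improves food security and HIV health outcomes". The last paragraph of the Background opens with a similar statement about testing impact, but then describes this study as exploring acceptability and feasibility and examining preliminary impacts. The opening of the Discussion gives the feasibility and preliminary-impact version.

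**The concern.** A comparison of the two arms is a comparison of Rongo with Migori. Any difference between the clinics that is unrelated to the intervention (patient mix, local economy, rainfall, clinic practice) enters the arm contrast in full. With a single clinic per arm, the data carry no information on how large such differences usually are.

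Low power is a different problem. An underpowered analysis gives wide intervals with the right coverage. Here the intervals lack a source of variance and so are too narrow for an intervention effect. Someone planning the next trial who has been told only that the pilot was underpowered would take its intervals as honest, if imprecise, bounds on the effect. A small p-value could likewise be taken as preliminary evidence of benefit when a site difference alone might have produced it. An aim worded as a test of improvement encourages that reading.

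**Working it through.** **Inputs from the article.** Clinics: 2, one per arm. Participants: 72 and 68. The article states no ICC, power or sample-size calculation, so there is no design figure to reproduce.

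**Assumed input.** ICC from 0.005 to 0.05.

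**Step 1: can site variance be estimated?** Between-clinic degrees of freedom = clinics − arms = 2 − 2 = 0. A site random effect is not identifiable, and a site fixed effect is the arm effect itself. Covariate adjustment can remove measured imbalance but cannot supply the missing variance.

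**Step 2: size of the omission.** Let s_b² and s_w² be the between-site and within-site variances, with ICC = s_b²/(s_b² + s_w²).

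- Variance of the arm difference, treating the two sites as independent draws: 2·s_b² + s_w²·(1/72 + 1/68).
- What an analysis without site variation uses: s_w²·(1/72 + 1/68) = 0.0286·s_w².
- Ratio = 1 + m·ICC/(1 − ICC), with m = 2/(1/72 + 1/68) = 69.9, taken as 70.
- Required SE multiplier = √ratio.
- Actual rejection rate of a nominal 5% test under no effect = 2·[1 − Φ(1.96/√ratio)].

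| Assumed ICC | Ratio | SE multiplier | Rejection rate under no effect |
|---|---|---|---|
| 0.005 | 1 + 70 × 0.005/0.995 = 1.35 | 1.16 | 9% |
| 0.01 | 1 + 70 × 0.01/0.99 = 1.71 | 1.31 | 13% |
| 0.02 | 1 + 70 × 0.02/0.98 = 2.43 | 1.56 | 21% |
| 0.05 | 1 + 70 × 0.05/0.95 = 4.68 | 2.16 | 37% |

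Coverage of a nominal 95% interval is 100% minus the last column: about 91% at ICC 0.005 and 63% at ICC 0.05. Using total rather than within-site variance as the reference changes little (multipliers 1.16, 1.30, 1.54 and 2.11).

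**Step 3: what the article's own baseline data show.** Statistical methods lists ordinary chi-square, rank-sum and t-tests for Table 2. As a check, sex exchange (ever), 15/72 against 28/68, gives an uncorrected chi-square p of 0.0091; the table prints 0.009. So this comparison behaves as an individual-level test with no site component. Table 2 holds 37 p-values, of which 10 are below 0.05: household income, sex exchange (ever), vegetables, meat and poultry, dairy, cooking fat, sweets, detectable viral load, physical health score and self-reported adherence. If all rows were exchangeable between sites, 37 × 0.05 = 1.85 would be expected. Five of the 10 are food-frequency items from one instrument, so the rows are correlated. The count illustrates that the sites differed before treatment; it is not a formal test.

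**Step 4: the aim.** Intervention model commits the pilot to testing whether outcomes improve. Analysis of outcome data says that it was not powered for formal testing of health, behavioural and empowerment outcomes, and the Discussion says that it was designed for feasibility and preliminary impact. These cannot all describe the same primary purpose, and zero between-site degrees of freedom rules out the first.

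**The case against.** The limitation is partly disclosed. The article says that the pilot was not powered for formal testing of its main outcomes, lists the two-site design first among its limitations, and leaves heterogeneity to a 16-site trial. That stands, and it narrows the gap to one missing statement: that the intervals describe within-site sampling only.

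The article nowhere says that participants are treated as independent, and the random effects for CD4 are left open. This also stands. The omission follows from the design and is not a modelling error that another method, or an unseen analysis plan, would repair.

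The size is uncertain. The sites were chosen for similar rainfall, health, topography and socioeconomic status, so two unrelated draws may overstate their difference. Several analyses use change or adjust for baseline, and the ICC for those outcomes may differ from that for raw levels. All this bears on the magnitude; the direction is the same for any positive ICC.

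Three stronger readings are tempting but unsupported. A reader might infer that the pilot's effect interval will set the size of the next trial; the article says only that it matters for planning, and does not derive the 16 sites from it. A reader might take the rejection rates above as properties of this trial; they are conditional on assumed ICCs. A reader might take Table 2 as direct proof of invalid outcome intervals; it shows correlated differences in baseline level, and says nothing about site variation in change.

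**Conclusion.** The point holds as a matter of design. Arm and clinic are fully confounded, between-site variance has zero degrees of freedom, and the planned tests and intervals exclude it under any model. The article attributes their weakness to power and to the need for replication, and assigns the intervals a planning role without this qualification.

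For ICCs of 0.005 to 0.05 with about 70 per site, the SE should be about 1.2 to 2.2 times larger and the nominal 5% test rejects about 9% to 37% of the time under no effect. These figures rest on an assumed ICC, on the sites behaving as independent draws, and on a normal approximation. The wording of the primary aim is a separate internal conflict that needs reconciling.

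**What to change.** 1. Reword the aim in Intervention model, and the matching opening of the last Background paragraph, to agree with the feasibility and preliminary-impact purpose stated later in the Background and in the Discussion. Present between-arm results as descriptive, preliminary estimates, and do not report between-arm p-values as tests of the intervention.

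2. State in Analysis of outcome data that the intervals are conditional on these two sites and exclude between-site variation. If a wider interval is shown, for example with the SE multiplied by √(1 + m·ICC/(1 − ICC)), label it a sensitivity analysis under an assumed ICC. It is not a corrected interval, because none can be computed from one clinic per arm.

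3. For planning the next trial, use the pilot for within-site standard deviations, baseline-to-follow-up correlations and retention. Take between-clinic variance from a stated ICC range or from external or routine clinic data, not from the pilot's between-arm interval.

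The cost is wording and, optionally, one sensitivity column per results table; no new pilot data are needed. The downside is that the intervals look less favourable and no significance claim is possible.

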## Results

### Screening and enrollment

Figure 3 describes study screening and enrollment numbers, along with reasons for participant ineligibility. We screened 142 and 154 adults, respectively at the intervention and control sites. We enrolled 72 and 68 participants at the intervention and control sites, respectively; four participants withdrew from the study, four from the intervention site and zero from the control site. One participant in the intervention arm failed to save the down payment necessary to receive the loan and was subsequently withdrawn from the study. The most common reasons for study ineligibility of screened participants included: did not have access to land or surface water, lived outside the study area, not on ART, and “other” reasons.

### Baseline characteristics of participants

At baseline (Table 2) participants at the intervention and control sites, respectively were similar in age (37 vs. 38 years), gender (51% female in both), education (19% vs. 18% completed secondary school) and marital status (75% vs. 79% married). Mental health and gender empowerment measures were similar among participants enrolled at the intervention and control sites. Reported monthly household income was lower among participants enrolled at the intervention in comparison to the control site (~$104) vs. (~$273), p = 0.008).

**Table 2 Tab2:** **Comparison of baseline sociodemographic, economic, sexual risk behavior, dietary intake, clinical, mental health, gender empowerment, clinical and laboratory findings of participants enrolled in**
***Shamba Maisha***
**at the intervention and control sites**

	**Intervention**	**Control**	**P-value**
	**N = 72**	**N = 68**	
**Sociodemographic variables**	n (%)	n (%)	
Mean age in years (SE)	37 (0.80)	38 (0.80)	0.16
Female gender	37 (51)	35 (51)	0.92
Education ≥ secondary school	14 (19)	12 (18)	0.82
Current married	54 (75)	54 (79)	0.25
Mean number of people in household (SE)	6 (0.2)	7 (0.3)	0.12
**Food security level**			
Moderately food insecure	14 (20)	14 (21)	0.86
Severely food insecure	57 (80)	53 (78)	0.86
Body Mass Index (BMI) <18.5	13 (18)	5 (7)	0.054
**Economic indicators**			
Mean (SE) Monthly Household Income (USD*)	104 (21.3)	273 (53.1)	0.008
Land ownership (Self or Jointly)	60 (83)	49 (73)	0.14
**Sexual risk behavior**			
Any unprotected sex	13 (18)	12 (18)	0.95
Sex exchange (ever)	15 (21)	28 (41)	0.009
Sex exchange (last 3 months)	2 (3)	6 (9)	0.12
>1 Sexual partners in the past 3 months	9 (13)	9 (13)	0.92
**Dietary intake (frequency of consumption - times/week)**			
Grains mean (SE)	19.0 (0.8)	20.8(0.8)	0.1320
Vege`s mean (SE)	20.3 (0.9)	25.9 (0.7)	<0.0001
Fruit mean (SE)	9.0 (0.6)	10.6 (0.9)	0.1352
Meat, Poultry mean (SE)	3.4 (0.3)	5.3 (0.3)	<0.00001
Eggs mean (SE)	0.9 (0.1)	1.3 (0.2)	0.117
Dairy mean (SE)	1.9 (0.3)	4.5 (0.5)	<0.0001
Cooking fat mean (SE)	5.0 (0.3)	6.8 (0.1)	<0.00001
Sweets mean (SE)	7.1 (0.7)	11.9 (0.7)	<0.00001
**Mental health**			
Depression score ≥1.75 (clinical depression)	1 (1)	4 (6)	0.2
Mental health summary score (SE)	57.1 (3.4)	42.8 (5.6)	0.15
Mean internalized AIDS related stigma scale (SE)	14.1 (0.2)	13.7 (0.2)	0.19
Disclosed to husband/wife/partner	65 (97)	63 (95)	0.68
Mean Social Support Score (SE)	53.4 (10.8)	35.8 (8.3)	0.2
Problem drinking based on audit C	1 (1)	2 (3)	0.53
**Gender empowerment**			
Mean sexual relationship power scale (women only) (SE)	54 (10)	47 (8)	0.59
Mean decision making dominance scale (SE)	46 (5)	42 (4)	0.46
**Clinical, Laboratory and antiretroviral (ART) adherence**			
WHO clinical stage 3 or 4	15 (21)	22 (33)	0.12
Median CD4 (IQR) cells/mm^3^	446 (330–629)	475 (356–679)	0.33
Baseline CD4 ≤ 350 cells/mm^3^	20 (29)	16 (24)	0.467
Viral load above the limit of detection (≥20 copies/mL)	34 (49)	19 (28)	0.010
Physical health summary score (SE)	54.3 (3.6)	45.5 (4.0)	0.03
Hospitalized in the last three months	3 (4)	5 (7)	0.4
Reported ART adherence per Visual Analogue Scale < 90%	0 (0)	6 (9)	0.01

*Converted Kenyan shillings (Ksh) to US dollar (85 Ksh/$).

A similar proportion of participants at the intervention and control sites reported moderate and severe food insecurity based on the HFAIS, although a greater proportion of participants at the intervention site had a low BMI in comparison to participants at the control site (18% vs. 7%, p = 0.054) (Table 2). In regards to dietary intake, participants enrolled at the intervention site reported less frequency of vegetable, meat/poultry, dairy, cooking fat, and sweets than participants enrolled at the control site (Table 2).

Twenty-one percent and 33%, respectively of intervention and control site participants had WHO stage 3 or 4 disease. While median CD4 count was similar between arms (intervention: 446 cells/mm^3^ vs. control: 475 cells/mm^3^, p = 0.33), a greater proportion of participants enrolled at the intervention arm had a detectable HIV viral load than participants enrolled at the control arm (49% vs. 28%, respectively, p < 0.010); Self-reported ART adherence < 90% per visual analogue scale was rare in both arms of the trial (Table 2).

